## Abstract

**Background:**

Individuals living in deprived inner cities have disproportionately high rates of cancers, Type 2 diabetes and obesity, which have stress- and physical inactivity-related etiologies. This study aims to quantify effects of ecological park restoration on physical activity, stress and cardio-metabolic health outcomes.

**Methods:**

The Study of Active Neighborhoods in Detroit is a quasi-experimental, longitudinal panel natural experiment with two conditions (restored park intervention (INT) and control (CNT)) and annual measurements at baseline and 3-years post-restoration. Individuals (sampled within 500 m of an INT/CNT park) serve as the unit of analysis. Restoration (*n* = 4 parks) involves replacing non-native plants and turf with native plants; creating trails; posting signage; and leading community stewardship events. The CNT condition (*n* = 5) is an unmaintained park, matched to INT based on specified neighborhood conditions. Recruitment involves several avenues, with a retention goal of 450 participants. Park measures include plant/avian diversity; usage of the park (SOPARC); signs of care; auditory environment recordings; and visual greenness using 360 imagery. Health outcomes include device-based physical activity behavior (primary outcome); salivary cortisol (secondary outcome); and several downstream health outcomes. Exposure to the INT will be assessed through visual contact time and time spent in the park using GPS data. Changes in health outcomes between years and INT versus CNT will be tested using generalized linear (mixed) models.

**Discussion:**

Our study will examine whether restored urban greenspaces increase physical activity and lower stress, with public health planning implications, where small changes in neighborhood greenspaces may have large health benefits in low-income neighborhoods.

**Study Registration:**

Registration: OSF Preregistration registered March 31, 2020. Accessible from https://osf.io/surx7.

## Background

Individuals living in socioeconomically deprived inner cities have disproportionately high rates of obesity, Type 2 diabetes, cancer and cardio-metabolic conditions, all of which have stress- and physical inactivity-related etiologies [1–14]. The cost of these diseases is enormous, where the direct annual medical costs for obesity exceed $300b [15], and societal tolls include declining or stagnating life expectancy, particularly in low-income communities [16]. Low-income neighborhoods experience dual risks, whereby physical activity (PA) levels are low and stress levels are high [17, 18]. Stress and physical inactivity can both lead to downstream inflammatory changes that alter body composition and metabolic and immune functions linked to chronic disease [19–22]. Studies underscore the twinned benefits of weight management and lowered stress that engaging in PA confers [23]. Lower stress, regardless of PA, assists with sustained weight loss [24] and improved cardio-metabolic health [25], making it an attractive goal for health benefits.

To induce change in PA and stress on a population level, researchers and city planners are exploring features of the built environment, such as greenspace (e.g., parks), that may promote healthy lifestyles [26, 27]. Parks serve as places to engage in PA in direct contact with nature — called ‘green PA’ — which has been shown to lower anxiety [28] and perceived stress [29, 30] over and above the effects of indoor PA [23] or outdoor PA without greenery [31]. In addition, cross-sectional research indicates that passive exposure to greenspace (e.g., visual, as in the sight of plants and trees, and auditory, as in birdsong) may lower stress [32, 33]. However, not all residents living near parks visit the parks or engage in PA, and, empirically, the relationship between neighborhood greenspace and PA is inconsistent (for a review [34]). Even so, greener neighborhoods consistently predict lower obesity rates across age groups and rural/urban settings [35–41]. One possible explanation for these findings is that healthier people simply choose to live in greener areas. Yet another possible explanation is that the greenness-obesity relationship is influenced not only by PA but by stress reduction.

To address these knowledge gaps, we designed the Study of Active Neighborhoods Detroit (StAND) to utilize a natural experiment (not a behavioral intervention) to illuminate the causal health effects of greenspace. We integrate leading-edge geospatial techniques to assess individual-level exposure to greenspace with longitudinal evaluation of device-based measures of PA and biomarkers of stress and cardio-metabolic health in low-income, predominantly African American individuals living in neighborhoods in Detroit, Michigan U.S.A.

### Objectives

The aims of StAND are to observe the effects of ecological restoration of parks on PA, stress and cardio-metabolic health outcomes from baseline through three-years post restoration using a quasi-experimental design. The hypotheses are:

#### Hypothesis 1

Compared to participants in control (CNT) park neighborhoods, participants in intervention (INT) park neighborhoods will have increased PA levels at three-years post-restoration.

#### Hypothesis 2

Compared to participants in CNT park neighborhoods, participants in INT park neighborhoods will have increased levels of ‘green PA’ at three-years post-restoration.

#### Hypothesis 3

Across both INT and CNT parks, the quality of visual and auditory exposures (positive and negative) will affect PA levels.

#### Hypothesis 4

Compared to participants in CNT park neighborhoods, participants in INT park neighborhoods will have lower stress levels as indexed by measures of cortisol, perceived stress, and anxiety at three-years post-restoration.

#### Hypothesis 5

Participants with higher levels of PA and ‘green PA’ will have lower stress.

#### Hypothesis 6

The quality of visual and auditory exposures (positive and negative) will affect stress levels.

#### Hypothesis 7

Compared to participants in CNT park neighborhoods, participants in INT park neighborhoods will have improved glycated hemoglobin A1C (A1C) and C-reactive protein (CRP) at three-years post-restoration.

#### Hypothesis 8

Compared to participants in CNT park neighborhoods, participants in INT park neighborhoods will have lower blood pressure, body mass index (BMI), and hip-to-waist ratios at three-years post-restoration.

## Methods

### Design

The overall design of StAND is a four-year quasi-experimental, natural experiment, with two conditions (INT and CNT), four measurement occasions, and individual-level measurement of exposures and outcomes (see Fig. 1 for a conceptual diagram for the study). Four INT parks were selected by Detroit Audubon and five comparable CNT parks were selected, based on size, existing trees/plants, and proximity to other bird habitats. All adults (i.e. aged ≥18 years) living in a CNT or INT park neighborhood (defined in the following text) were invited to participate. Baseline (t = 0) and three annual measurements (t = 1 to t = 3) post-restoration will be conducted on participating individuals with the intention of having a longitudinal panel study design. However, we considered sampling alternatives depending on attrition, as others studies have done [42]. If attrition is higher than expected (> 25% at t = 1), then additional participants will be recruited at each time point, yielding a repeated cross-sectional design, with a nested panel. If assessments at certain time points are missing within the panel for some participants, we will assume that data from our unbalanced panel is missing at random.

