### Participants

Participants are adults who reside in a study park’s zone of influence, which is deemed to be 0.5 km (0.31mi), which is an approximate 15-min walk to the park and also a reasonable maximum distance for hearing birdsong in an urban setting [45]. Participants will be recruited from within a 16-cell grid (120m^2^/cell) around each park. Thus, the unit of measurement is the individual, but the unit of assignment-to-intervention is neighborhood. We conducted a pilot study in two neighborhoods in 2018 (*n* = 67 participants enrolled) and received funding at the end of the summer in 2019, yielding a truncated field season (*n* = 145 participants). The first full field season for this study will be 2020. To recruit participants, we mail postcards and conduct recruitment activities (e.g., information booths) in each neighborhood. Field staff then visit homes in each study neighborhood to brief potential participants on the study, request participation, and screen for inclusion. We recruit only one English-speaking male or female (≥ 18y) without mobility issues per household, which is at the household’s discretion. To ensure participant comprehension and confirm contact information, we use an electronic text message to finalize enrollment. Participants are then instructed on the correct usage of the accelerometer (Actigraph GT3X), Global Positioning System (GPS) device (Canmore) and cortisol sample collection and instructed that a study shuttle will take them to their scheduled health appointment in our study office. The target total sample is 450 adults to be recruited and retained. To retain participants, we will employ a set of strategies including: 1) sending holiday cards with neighborhood-level results; 2) sending birthday cards; and 3) sending periodic, brief surveys through StANDApp.

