#### Risk of bias assessment

This study employs the Risk Of Bias In Non-randomized Studies of Interventions (ROBINS-I) tool [53] to assess risk of bias for the pre-intervention components. Specifically, we aimed to reduce bias due to confounding by: i) including a suite of potential individual-level confounders in our survey instrument (detailed below); ii) matching INT and CNT neighborhoods based on baseline area-level factors which may influence both the outcomes and the exposures of interest (detailed above); and iii) consideration of potential co-interventions that might occur (that are related to receiving the intervention and the outcomes). The potential for the intervention to lead to gentrification was identified. Specific items in the surveys will measure perceptions of gentrification and median home price in each study neighborhood will be quantified using publically available data from Redfin, a national real estate brokerage, for each time point. At the time of the intervention, bias in the classification of the intervention will be minimized by collecting objective data on: park usage, plant species, bird species, greenness and signs of care. Post-intervention bias will be assessed at the conclusion of the study.

The participants and the study staff collecting outcome data will be blinded to the condition assignment. This will be accomplished by referring to neighborhoods using a three-letter code and restriction of information about the intervention locations. We will assess blinding at the end of each field season by asking staff which neighborhoods they believe are receiving the intervention. Success will be determined as either i) a majority of “don’t know” responses; or ii) a balance between correct and incorrect responses. Because this is a natural experiment and the researchers have no control over whether the intervention is carried out completely in all locations and to what degree the intervention is discussed throughout the neighborhoods, assessment of blinding of participants is not appropriate.

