### Survey

Basic demographic data information (age, sex, ethnicity, employment, household composition, length of residence) will be collected at recruitment or when re-contacted at each timepoint. Then, each participant will complete a self-administered paper survey in the privacy of their own home to assess: income, perceptions of the neighborhood [98–102], disease and prescription medication history [103–106], diet [107, 108], perceived stress [74], anxiety and depression symptoms [72, 73] (discussed previously), nature-relatedness [109]; all which were considered potential correlates of device-based PA and stress. Questions about the perceptions of the social and environmental features of neighborhoods have been shown to have moderate to high agreement (rho range = 0.42–0.91) [99]. Family Life, Activity, Sun, Health, and Eating (FLASHE) questions related to diet were reviewed by the scientific experts for consistency with existing, validated measures [108]. The nature-relatedness scale (NR-6) has been shown to demonstrate good internal consistency, temporal stability, and predict happiness, environmental concern, and nature contact [109]. Measures that may serve as confounders include: 1) symptoms of acute illness or infection or prescription medication which could influence biomarker measures; 2) attitudes toward nature using the NR-6, because these may influence behaviors; and 3) perceived safety which may influence stress [110], PA [111, 112], and park usage [113].

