We will compare INT and CNT groups from baseline through three-years post-restoration for changes in blood pressure, hip-to-waist ratio and BMI (continuously measured) between INT and CNT groups.

Despite our best effort to recruit and retain a longitudinal panel of participants, we may face problems with attrition higher than the projected attrition rates of 15% at t = 1, another 10% at t = 2, and 5% at t = 3. With these levels, our longitudinal panel becomes unbalanced but valid inference can be made under the assumption that attrition is at random (MAR). We describe another strategy, *repeated cross-sections*.

By repeated cross-sections we mean a series of independent samples are drawn at the subsequent times t = 1, 2, 3 following the initial baseline sample at t = 0. It could happen that a participant in the baseline sample is also in any of the subsequent samples, but this is at random. With repeated cross-sectional samples, we cannot estimate *within participant* change in outcomes, which is the key advantage of the longitudinal panel approach. However, we can still assess patterns of change at an aggregate level as explained in the following text.

Consider an outcome $$ {\mathit{\mathsf{Y}}}_{\mathit{\mathsf{it}}} $$ at time *t* in the *i-*th participant, and the linear model $$ {{\textsf{Y}}}_{{\textsf{i}\textsf{t}}}={\mathbf{\textsf{x}}}_{{\textsf{i}\textsf{t}}}^{\prime}\beta +{\alpha}_{{\textsf{i}}}+{\varepsilon}_{{\textsf{i}\textsf{t}}} $$ with exogenous covariates $$ {\mathbf{\textsf{x}}}_{{\textsf{it}}} $$, *t* = 0, 1, 2, 3. We aggregate each sample into *C* cohorts defined as participants who share common characteristics such as age, sex, neighborhood park, etc. Aggregation of participants to the cohort level *c* replaces the model by the cohort model $$ {\overline{{\textsf{Y}}}}_{{\textsf{c}\textsf{t}}}={\overline{{\mathbf{\textsf{x}}}^{\prime}}}_{{\textsf{c}\textsf{t}}}\beta +{\overline{\alpha}}_{{\textsf{c}}}+{\overline{\varepsilon}}_{{\textsf{c}\textsf{t}}} $$, *c* = 1, …,*C*, *t* = 0, 1, 2, 3. (Bar notation refers to averages over participants within cohort/time). Our observed data become a pseudo-panel of repeated observations on cohorts over time, and estimation of differences between INT and CNT cohorts could be compared over time, although the cohorts are not comprised of the same participants from one time point to the other. Some technical issues will need to be addressed to ensure a consistent estimator of *β* [143–146].

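### Post-restoration top-up recruits need only current residence, so the difference-in-differences could mix who lives near restored parks with residents' health

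*Protocol article*

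**What the plan says.** The planned design is a panel with a baseline and "three annual measurements (t = 1 to t = 3) post-restoration" (Protocol article, Design). Loss above 25% at t = 1 activates a fallback: "additional participants will be recruited at each time point, yielding a repeated cross-sectional design, with a nested panel".

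The residence criterion is in the Participants section: "Participants are adults who reside in a study park’s zone of influence, which is deemed to be 0.5 km". The other criteria there are one English-speaking adult per household, without mobility issues. No move-in date or minimum stay is printed, and no separate rule is given for people recruited later.

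The Risk of bias assessment section states: "The potential for the intervention to lead to gentrification was identified". Its response is to measure residents' perceptions and median home prices. It does not say how either would enter the outcome models.

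In the Statistical analysis section, repeated cross-sections are described as independent samples at t = 1, 2 and 3. They are analysed as a pseudo-panel of "cohorts defined as participants who share common characteristics such as age, sex, neighborhood park, etc". The Survey section lists, among the basic demographic items, "length of residence) will be collected at recruitment or when re-contacted at each timepoint". The only analytic use named for that item is the comparison of INT with CNT at baseline.

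**The concern.** The Background names a rival explanation for the link between greenness and health: healthier people may choose greener places. The natural experiment is meant to get past it. Under the fallback, someone who moved in after restoration can be recruited and enter the INT mean at t = 1, 2 or 3. If such people are more common near INT parks than near CNT parks, and differ from established residents in activity or stress, the group-by-time contrast moves even when no resident has changed. The causal reading of the primary comparison is at stake, but only if the fallback is activated.

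**Working it through.** Arithmetic cannot show whether selection will occur. It can only size it under assumptions.

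**1. The plan's own figures (Sample size section).** Attrition: 620 × 0.85 × 0.90 × 0.95 = 450.6, which reproduces 450. Power inputs: effect 0.35; 200 INT and 250 CNT participants (m = 50 per park, 4 and 5 parks); r = 0.35; ρ = 0.004; two-sided 5%. Normal approximation, with 1/200 + 1/250 = 0.009:
- Change variance 2[(1 − r) + (m − 1)ρ] = 2(0.65 + 0.196) = 1.692; SE = √(1.692 × 0.009) = 0.123; power 81.0%.
- Change variance 2(1 − r)[1 + (m − 1)ρ] = 1.3 × 1.196 = 1.555; SE = √(1.555 × 0.009) = 0.118; power 84.1%.

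The stated 82% lies between the two. Both assume a panel.

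**2. Can an in-mover enter, and does anything catch it?**
- Top-up happens at t = 1 to 3, all after restoration. Eligibility is current residence. A post-restoration arrival therefore qualifies.
- The equivalence check is made at baseline under the panel assumption. In-movers have no baseline record, so it cannot see them.
- The general promise to adjust for unbalanced factors names no residence variable.

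**3. Where the bias lands.** The cohort model gives each cohort a mean individual effect with no time index. Because park is one of the example cohort traits, a cohort so defined lies wholly in INT or wholly in CNT. If its composition shifts, the effect becomes a constant plus a drift over time. The INT-minus-CNT change in that drift is the same contrast as the difference-in-differences, so the model cannot separate them.

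**4. Share of top-ups at t = 3 (f).** The article sets no refill target. Taking 450 as the target, and the planned 10% and 5% losses after t = 1:
- 25% loss: 620 × 0.75 × 0.90 × 0.95 = 397.6 remain; f = (450 − 397.6)/450 = 0.117
- 35% loss: 344.6 remain; f = 0.234
- 50% loss: 265.1 remain; f = 0.411

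Refilling to 620 after 25% loss gives f = (620 − 397.6)/620 = 0.359.

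**5. Bias.** Bias = f × (p_INT − p_CNT) × d, where p is the in-mover share of new recruits and d is the in-mover minus established-resident difference in SD. Neither is in the documents. Assumed: p_INT = 0.30, p_CNT = 0.10, d = 0.3 to 0.5, and the same f in both arms.

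| Scenario | f | Bias, d = 0.3 | Bias, d = 0.5 | Share of 0.35 |
|---|---|---|---|---|
| 25% loss, refill to 450 | 0.117 | 0.007 | 0.012 | 2-3% |
| 35% loss, refill to 450 | 0.234 | 0.014 | 0.023 | 4-7% |
| 25% loss, refill to 620 | 0.359 | 0.022 | 0.036 | 6-10% |
| 50% loss, refill to 450 | 0.411 | 0.025 | 0.041 | 7-12% |
| Wholly fresh t = 3 sample | 1 | 0.060 | 0.100 | 17-29% |

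A wider range: if in-movers exceed CNT by 5-30% of the analysed INT sample and d is 0.25-1.0 SD, the bias runs from 0.05 × 0.25 = 0.0125 to 0.30 × 1.0 = 0.30 SD, or 4-86% of 0.35. The upper end cannot arise at the trigger with a refill to 450, where top-ups are only about 12% of the sample.

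**6. Against sampling error.** At the trigger, 0.007-0.012 SD is 0.06-0.10 of the panel SE of 0.118. Fresh samples lose the serial correlation. With r = 0 both variance forms give 2 × 1.196 = 2.392 and SE = √(2.392 × 0.009) = 0.147, so 0.06-0.10 SD is 0.41-0.68 of an SE.

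**The case against.** The fallback may never be used: projected loss at t = 1 is 15% and the trigger is 25%. Even then a nested panel remains, in which in-movers cannot create change. Attitudes to nature and length of residence are collected. The article promises adjustment for unbalanced factors, robustness checks, and an assessment of post-intervention bias at the end of the study. It concedes that repeated cross-sections show only aggregate change, and its hypotheses refer to participants in park neighborhoods, not specifically to those living there before restoration. Detailed cohort definitions for a contingency are commonly left to a fuller document.

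Much of this stands, and it bounds the point. Several stronger readings that a reader might infer are not supported:
- That there is no residence requirement. There is one; what is absent is residence before restoration.
- That newcomers will certainly be counted as a health effect. The data needed to separate them exist; no stated rule uses them that way.
- That the bias favours the intervention. It does so only if in-movers have better outcomes, and shorter exposure among newcomers could dilute an effect.
- That the pseudo-panel fails because people age out of their cohort. The traits are given as examples, and birth-year bands are not excluded.
- That a newcomer at t = 3 is misclassified. The three years can be read as dating the park, and individual contact is measured separately.

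What the objection does not remove is that the article prints the trigger, the eligibility rule and the form of the model. Together they leave the main contrast open to a change in population that the article itself foresees.

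**Conclusion.** The concern holds in a conditional form. If top-up is activated, the difference-in-differences could combine neighborhood turnover with residents' health change, and no stated check separates them. Bias requires in-movers to be more frequent in one arm and to differ in outcome; the documents quantify neither and fix no direction. Under the 30% versus 10% and 0.3-0.5 SD assumptions it is negligible at the trigger with a refill to 450 (0.007-0.012 SD). It becomes material at 0.06-0.10 SD, or 17-29% of the design effect, if the t = 3 sample is wholly fresh, as the repeated cross-sections text describes. The change is worth making because it is cheap and protects the causal question, and it should be settled before any top-up begins. It does not invalidate the planned panel analysis.

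**What to change.** In the Design section and the repeated cross-sections part of Statistical analysis:
- Limit the primary analysis of post-baseline recruits to adults who lived in the same park zone before one calendar date preceding the first restoration. Use the same date for all nine parks. Park-specific dates borrowed from a matched park would not work, since 4 INT and 5 CNT parks have no stated pairing.
- Derive this from the length of residence already collected. Confirm that the item captures time in the zone and not only at the current address, which the article does not say.
- Define pseudo-panel cohorts by fixed traits (birth-year band, sex, park) among these residents.
- Report the nested-panel difference-in-differences alongside, and describe newcomers separately as neighborhood change.

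The cost is protocol wording and, if needed, one screening question. The pool for top-up is somewhat smaller, and the result then applies to established residents. The rule does not address selective out-migration, which still rests on the missing-data assumptions.
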